### Randomization and blinding

The double-blind method will be used for all aspects of this study including the enrolment of participants, investigators, care providers, outcome assessors, and data analysts. A statistician labelled and distributed the study drugs to each site. A study coordinator will be blinded and participants will be assigned in a 1:1 ratio to treatment groups based on the SAS Analytics Software Solutions (version 9.4, SAS Institute Inc., Cary, North Carolina 27,513, US), it will be used to generate random codes using the stratified randomization method. The study center will be the stratification factor. Pharmacists at the pharmacies of all sites of the clinical trial will be blinded to the patient characteristics and will distribute drugs to the patients according to the instructions of the investigators. The selected block length and random initial value seed parameters will be considered confidential data.

#### Research contents

The lung function index, blood oxygen saturation, and quality of life will be continuously monitored and recorded for each subject (Fig. 1).

Lung function parameters will be measured are as follows, including vital capacity (VC), total vital capacity (TLC), FVC, FLV, FVC%, DLCO, and predicted diffusion capacity for carbon monoxide (DLCO%). Furthermore, FEV1, residual volume (RV), maximum vital capacity (MVV), expiratory reserve volume (ERV), inspiratory reserve volume (IRV), peak expiratory flow (PEF), maximal middle expiratory flow (MMEF), tide volume (VT), and inspiratory capacity (IC), will be also measured, among others.

Detection of blood oxygen saturation will be determined through arterial blood oxygen saturation (SaO_2_) and partial pressure of oxygen (PaO_2_), among other indicators measured using a pulse oximeter.

A 6-min walking distance test will be conducted to assess lung function according to the American Thoracic Society (ATS) criterion.

#### Dyspnea assessment: elevated Borg dyspnea score

SGRQ: SGRQ will be used to evaluate the impact of chronic airflow limitation on the quality of life. The questionnaire contains 50 items, including symptoms, activity ability, and the impact of the disease on daily life, which will be scored over a range of 0–100 points. The higher the score, the worse the health status of patients.

#### Quality of life assessment

SF-36 table, SCL-90 table, SAS table, and SDS table will be constructed to assess the quality of life.

#### Investigational drug

##### Therapeutic schedule

In this study, TCM experts will identify and select the research subjects with Qi-Yin deficiency based on TCM syndrome differentiation, while experts in modern medicine will formulate the drug prescription and design a treatment plan. All subjects will be randomly divided into a treatment or control group in a 1:1 ratio. The treatment group will receive modern medicine + TCM herb granule 1, while the control group will be treated using modern medicine + TCM herb granules (placebo). During treatment, the dosage of the TCM herb or pirfenidone was not adjusted for any subject.

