##### Drug preparation and treatment program

The treatment of pulmonary fibrosis will be in adherence to "The 2018 Diagnosis of Idiopathic Pulmonary Fibrosis Guidelines" as symptomatic treatment is indispensable for patients with pulmonary fibrosis [34–36]. Drugs including pirfenidone, acetylcysteine, and glucocorticoids, which have been proven to be efficacious in the treatment of pulmonary fibrosis will constitute the modern drugs in this study.

TCM herb granule 1 will be will be formulated as mixed granules for single TCM herb administration and packed in food-grade plastic bags (8 g/bag), the granules will comprise extracts of adenophora tetraphylla, radix glehniae, liriope graminifolia, codonopsis pilosula, selfheal, meretricis, angelica sinensis, arrowhead mushroom, oysters, seaweed, peach kernel, the root of red-rooted salvia, curcuma aromatica, rhizome sparganii, radices zedoariae, and radix astragali. TCM herb granules 2 is placebo and will be formulated using supplementary materials, and it will be packed in food-grade plastic bags (8 g/bag) (Table 1). The method of use of each drug is shown in Table 1.

**Table 1 Tab1:** Therapeutic regimen of this study

Drug	Dosage	Taking drug	Remarks
Pirfenidone	The initial dosage is 200 mg/time, 3 times/day; and then add the dose to 600 mg/time by 200 mg/day. Finally, the dose is 600 mg/time, 3 times/day for 12 months	Take it half an hour after breakfast, lunch and dinner, respectively	Drug must be used for each participant
Acetylcysteine	200 mg/time, 3 times/day for 12 months	Take it half an hour after breakfast, lunch and dinner, respectively	Selective use for all subjects
Glucocorticoid	0.5 mg × kg^−1^ × day^−1^ for 1 month, and then 0.25 mg × kg^−1^ × day^−1^ for 2 months, and then the dose decline to 0.125 mg × kg^−1^ × day^−1^ for 12 months	Take it half an hour after breakfast, lunch and dinner, respectively	Selective use for all subjects
Chinese medicine granules 1	8 g/bag, 2 bags/ time, 3 times/day for 12 months	Take this granula after mixing it with water, take it half an hour after breakfast, lunch and dinner, respectively	Drug must be used for each individual in treatment group
Chinese medicine granules 2	8 g/bag, 2 bags/time, 3 times/day for 12 months	Take this granula after mixing it with water, take it half an hour after breakfast, lunch and dinner, respectively	Drug must be used for each volunteer in control group

*kg* kilogram, *mg* milligram

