##### Dispensing the herbal medication

Each center will have a drug administrator who is responsible for the storage, distribution, recovery, record keeping, and retrieval of the experimental drugs. The modern medicine + TCM or modern medicine + TCM placebo will be provided to patients based on the enrollment sequence. The modern medicine + TCM or modern medicine + TCM placebo administered to patients will remain unchanged throughout the study. The test drugs will be distributed in each follow-up after the beginning of the study, and the leftover drugs will be recovered in the next drug allocation.

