#### Safety indices

It is necessary to pay close attention to any changes in the relevant safety indicators during treatment as certain therapeutic drugs (especially herbs) may cause organ damage. The safety indices include body temperature, blood pressure, heart rate, respiration, height, and weight, among others[37] (Table 2). Upon and after recruitment, the safety indices of all subjects will be determined several times during the 12-month treatment procedure.

**Table 2 Tab2:** Safety indexes will be detected for each volunteer in the study

Classification	Index	Detection time point
Blood routine	Red blood cell, hemoglobin, white blood cell, white blood cell classification count, hematocrit, platelet, etc	When one volunteer will be recruited, these safe indexes will be detected for five times (0 month, 3rd month, 6th month, 9th month, 12th month) across whole study
Urine routine	PH, urine specific gravity, urobilinogen, urine blood, white blood cell, urine protein, glucose in urine, bilirubin, ketone body, urine red blood cell, etc	
Liver function	Total protein, globulin, albumin, alanine aminotransferase, aspartate aminotransferase, total bilirubin, direct bilirubin, indirect bilirubin, urine bilirubin, urobilinogen, serum bile acid, gamma glutamyltranspeptidase, alkaline phosphatase, etc	
Kidney function	Serum urea, uric acid, blood β-microglobulin, serum creatinine, etc	
Blood sugar	Fasting blood sugar	
Electrocardiogram	Chest leads, limb lead	

*PH* hydrogen ion concentration

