### Suspension of protocol

Participation of a patient in the clinical trial may be prematurely terminated under the following circumstances: (1) death of the participant, (2) failure to obtain consent to the continuation of the clinical trial, and (3) refusal to continue the clinical trial by formerly incapacitated patients who have regained their ability to provide consent.

The principal investigator have the power to pause or terminate the clinical trial in a trial center in coordination with the Safety Committee and the biometrician for a number of reasons. These include if (1) serious safety problems occur during the study period. (2) The drug efficacy is found to be poor or ineffective midway during the study. 3) Major errors or flaws are detected in the trial design. (4) The research team requests the termination of the study for reasons including, but not limited to, funding, management, or a lack of study subjects for recruitment. (5) The administrative department cancels the study.

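### The no-adjustment rule for the herb and pirfenidone carries no safety exception, although the plan expects possible organ damage and tests for it during treatment

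*Protocol article*

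**What the plan says.** Under *Therapeutic schedule*, the protocol article sets the dosing rule for both main drugs in one sentence: "During treatment, the dosage of the TCM herb or pirfenidone was not adjusted for any subject".

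Table 1, under *Drug preparation and treatment program*, gives pirfenidone (after a run-up) and the granules at fixed doses for 12 months. Its remarks column says of pirfenidone "Drug must be used for each participant" and of granules 1 "Drug must be used for each individual in treatment group". Acetylcysteine and glucocorticoid carry the remark "Selective use for all subjects". *Dispensing the herbal medication* says that the assigned combination "administered to patients will remain unchanged throughout the study".

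*Safety indices* explains why safety is monitored: "certain therapeutic drugs (especially herbs) may cause organ damage". Table 2 lists blood, urine, liver, kidney, fasting glucose and electrocardiogram measures, and says that "these safe indexes will be detected for five times", at months 0, 3, 6, 9 and 12.

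*Suspension of protocol* lets the trial be paused or ended in a centre if "serious safety problems occur during the study period".

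**The concern.** Safety tests during treatment are useful if someone can act on the result. Here the article anticipates organ damage and schedules tests that could detect it, yet its only rule on individual dosage is that dosage does not change. An investigator with an abnormal liver or kidney result at month 3, 6 or 9 who wants to lower the dose finds a sentence that rules this out.

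Patient safety is at stake first. Consistency comes second: an investigator who follows the sentence literally will keep the full dose or stop altogether, while another may reduce the dose and depart from the printed rule. In a multicentre trial planned for 514 subjects, the article should not leave that to interpretation.

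**Working it through.** The plan has no figure to reproduce on this point. The check sets the sections side by side.

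1. **Scope of the dosing sentence.** It covers the herb and pirfenidone, applies to every subject and has no qualifier. Table 1 raises pirfenidone from 200 mg to 600 mg per dose for everyone, so the sentence can sensibly mean only that there is no *individual* adjustment. A reduction for toxicity is an individual adjustment and is therefore excluded as written.

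2. **Timing of the tests.** Table 2 gives five test times. Month 0 precedes treatment and month 12 is its end, taking the 12 months from the start of treatment (an assumption). That leaves 5 − 2 = 3 tests, at months 3, 6 and 9, with 12 − 3 = 9, 12 − 6 = 6 and 12 − 9 = 3 months of treatment still to come. These are the occasions on which a dose rule for an abnormal result would be used.

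3. **Does another section restore dose reduction for one patient?**
   - *Subject compliance and drug inventory*: missed or insufficient doses go into the case report form to judge compliance. This records a departure from full dose but does not permit one, and it gives no separate category for a reduction ordered for safety.
   - *Participant withdrawal*: a subject may leave at any time, but study measures then cease. This ends follow-up and does not change a dose.
   - *Suspension of protocol*: the safety clause acts on the trial in a centre. The patient-level list covers death and two consent-related reasons, and concerns participation, not dose.
   - *Data management and monitoring*: the independent board oversees the safety of the trial as a whole.

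   None of these permits a lower dose for an individual subject.

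4. **How much do Table 1 and the dispensing text add?** Little. The mandatory remarks, set against the selective ones, most naturally separate required components of the regimen from optional ones. The dispensing sentence follows a statement about supply by enrolment order and most likely concerns which treatment was allocated. The point therefore rests on the *Therapeutic schedule* sentence set against *Safety indices*.

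**The case against.** The strongest reply is that this is a condensed article. Toxicity thresholds and stopping rules usually sit in the full protocol, which is not shown, and their absence here is no fault. On this view the sentence, written in the past tense at the end of a paragraph on syndrome selection and group assignment, means only that dosing is fixed and not tailored to the individual. A fixed dose with stopping for toxicity is an ordinary design. The article also has safeguards: severe liver and kidney dysfunction is excluded at entry, tests are repeated, withdrawal is free, and a safety committee and an independent board exist.

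Much of this stands. Detailed thresholds may be left to the full protocol, and a fixed regimen needs no defence. The reply does not dispose of the sentence itself, which is a positive, universal statement and not a silence. The surrounding text describes planned treatment, so the past tense does not turn it into a report of something already done. If the full protocol does allow reductions for toxicity, the article contradicts it. If it does not, the rule needs an exception. The sentence should be changed in either case.

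A reader might infer more: that a subject with organ toxicity must keep taking the drug, or that toxicity cannot end a subject's participation. The documents do not support either reading. Interrupting or stopping drug is nowhere forbidden, and the patient-level list under *Suspension of protocol* is not said to be exhaustive.

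**Conclusion.** The point holds in a narrow form. As printed, the article excludes a dose reduction of the herb or pirfenidone for toxicity in an individual subject, while expecting possible organ damage and testing for it three times during treatment. It is a stated rule that lacks a needed exception.

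Its size cannot be given as a number of subjects, because the article reports no toxicity rate for either drug. Nor is there a basis for claiming unequal loss between the arms, or any bias in the primary comparison. The conclusion assumes that the sentence describes planned conduct and that no safety exception is printed elsewhere in the article. It makes no assumption about what the full protocol contains. It ranks as a cheap improvement on patient-safety grounds.

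**What to change.** - **Dosing sentence.** In *Therapeutic schedule*, add an exception for safety reasons. Say that pirfenidone or the granules may be reduced, interrupted or discontinued for adverse events or abnormal Table 2 results. Thresholds may stay in the full protocol.
- **Follow-up and analysis.** State that subjects who reduce or stop drug for safety and still consent are followed to month 12 and kept in the full analysis set named under *Database*. Changing the drug should not by itself end participation.
- **Recording.** In the case report form, enter the date and reason of a safety-driven change separately from missed or insufficient doses, so that it is not counted as non-compliance.

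The cost is one amended sentence, one added sentence on follow-up and analysis, and one form entry for date and reason. No extra visits or tests are needed. The downside is that some month-12 data will come from subjects off full dose.

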##### Drug preparation and treatment program

The treatment of pulmonary fibrosis will be in adherence to "The 2018 Diagnosis of Idiopathic Pulmonary Fibrosis Guidelines" as symptomatic treatment is indispensable for patients with pulmonary fibrosis [34–36]. Drugs including pirfenidone, acetylcysteine, and glucocorticoids, which have been proven to be efficacious in the treatment of pulmonary fibrosis will constitute the modern drugs in this study.

TCM herb granule 1 will be will be formulated as mixed granules for single TCM herb administration and packed in food-grade plastic bags (8 g/bag), the granules will comprise extracts of adenophora tetraphylla, radix glehniae, liriope graminifolia, codonopsis pilosula, selfheal, meretricis, angelica sinensis, arrowhead mushroom, oysters, seaweed, peach kernel, the root of red-rooted salvia, curcuma aromatica, rhizome sparganii, radices zedoariae, and radix astragali. TCM herb granules 2 is placebo and will be formulated using supplementary materials, and it will be packed in food-grade plastic bags (8 g/bag) (Table 1). The method of use of each drug is shown in Table 1.

**Table 1 Tab1:** Therapeutic regimen of this study

Drug	Dosage	Taking drug	Remarks
Pirfenidone	The initial dosage is 200 mg/time, 3 times/day; and then add the dose to 600 mg/time by 200 mg/day. Finally, the dose is 600 mg/time, 3 times/day for 12 months	Take it half an hour after breakfast, lunch and dinner, respectively	Drug must be used for each participant
Acetylcysteine	200 mg/time, 3 times/day for 12 months	Take it half an hour after breakfast, lunch and dinner, respectively	Selective use for all subjects
Glucocorticoid	0.5 mg × kg^−1^ × day^−1^ for 1 month, and then 0.25 mg × kg^−1^ × day^−1^ for 2 months, and then the dose decline to 0.125 mg × kg^−1^ × day^−1^ for 12 months	Take it half an hour after breakfast, lunch and dinner, respectively	Selective use for all subjects
Chinese medicine granules 1	8 g/bag, 2 bags/ time, 3 times/day for 12 months	Take this granula after mixing it with water, take it half an hour after breakfast, lunch and dinner, respectively	Drug must be used for each individual in treatment group
Chinese medicine granules 2	8 g/bag, 2 bags/time, 3 times/day for 12 months	Take this granula after mixing it with water, take it half an hour after breakfast, lunch and dinner, respectively	Drug must be used for each volunteer in control group

*kg* kilogram, *mg* milligram

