#### Information collection from participants during each follow-up

Each subject enrolled in the study will be followed-up once every 3 months and the described indices will be determined each time. A total of 5 (months 0, 3, 6, 9, and 12) determinations per subject will be made during the study period.

In each follow-up, a structured questionnaire will be used to collect clinical information and indices. These included cough, expectoration, fatigue, chest tightness, chest pain, dyspnea, insomnia, emaciation, loss of appetite, VC, TLC, FVC, FVC%, DLCO, DLCO%, FEV1, RV, MVV, RV/TCL, ERV, IRV, PEF, MMEF, VT, IC, 6-min walking distance, Borg dyspnea score, and TCM syndrome scores, which are reflective of respiratory function and will help determine TCM syndrome scores. Moreover, the SCL-90, SF-36, SAS, and SDS scales will be used to record and measure quality of life for each individual during every follow-up.

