## Limitations of this study

Our study has several shortcomings that may need to be addressed. First, this is a multi-center randomized controlled trial conducted over a 12-month period. Therefore, the long-term outcome of the treatment and control groups may not be obtained in a short time. Second, the components of TCM are complex and diverse, and these components are used as a mixture. Hence, it is difficult to identify or separate single chemical compounds from the complex mixture of herbs that are used to treat pulmonary fibrosis. Additionally, the mechanism of TCM in the prevention and treatment of pulmonary fibrosis is complex, and the mechanism of the interaction between TCM and modern medicines remain unclear. Hence, a large-sample, longstanding, double-blind RCT may have to be conducted to determine the long-term outcomes for different treatment plans. In addition, the principal components responsible for activity will have to be identified and extracted from herbs and further developed, following which, their efficacy in treating pulmonary fibrosis should be examined in future RCTs.

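### The glucocorticoid schedule in Table 1 adds up to 15 months in a 12-month trial, leaving 3 scheduled months of dosing after the last planned safety test

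*Protocol article*

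**What the plan says.** The section on drug preparation and treatment program refers the reader to Table 1 for how each drug is used, so the table is the dosing instruction. Its glucocorticoid row has three steps:

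- "0.5 mg × kg^−1^ × day^−1^ for 1 month"
- "and then 0.25 mg × kg^−1^ × day^−1^ for 2 months"
- a last step at 0.125 mg/kg/day, so that the row ends "for 2 months, and then the dose decline to 0.125 mg × kg^−1^ × day^−1^ for 12 months".

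The remarks column marks the drug "Selective use for all subjects", so it is optional background treatment, available in both arms. The acetylcysteine row and both granule rows of Table 1 run for 12 months. The pirfenidone row has a short dose build-up followed by 12 months at full dose.

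The rest of the article describes a 12-month trial:

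- Safety indices: the indices "will be determined several times during the 12-month treatment procedure".
- Table 2: "these safe indexes will be detected for five times (0 month, 3rd month, 6th month, 9th month, 12th month) across whole study".
- Information collection during each follow-up: "A total of 5 (months 0, 3, 6, 9, and 12) determinations per subject will be made during the study period".
- Limitations: "this is a multi-center randomized controlled trial conducted over a 12-month period".

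No visit or safety test after month 12 is described.

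**The concern.** The steps in the glucocorticoid row follow one another, and each is given its own length. Taken as written, they run past the end of the trial. A prescriber following the table cannot tell whether the lowest dose is to be given for 9 months, ending with the trial, or for 12 months, ending three months after it.

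What is at stake is safety follow-up. Table 2 schedules blood counts, liver and kidney function, fasting blood sugar and an electrocardiogram, all for the last time at month 12. The safety section itself asks for close attention to these indicators during treatment. On the literal reading, steroid-treated patients would stay on drug for months with no planned test and would have none at the end of dosing.

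The point does not touch the sample size, the primary analysis or the treatment comparison. Dosing after month 12 cannot change outcomes measured between months 0 and 12.

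**Working it through.** **Inputs from the article**

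- Steps in Table 1: 1 month at 0.5, 2 months at 0.25 and 12 months at 0.125 mg/kg/day.
- Treatment length and last safety test: 12 months and month 12 (Safety indices, Table 2, follow-up section, Limitations).
- Planned sample: 514 (Sample size calculation).

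**Assumptions**

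- The drug starts at month 0. The article gives no separate start time for it. A later start would lengthen the overrun.
- A month has 30 days.

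**Duration**

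- Scheduled length = 1 + 2 + 12 = 15 months. The trial's own figure of 12 months is not reproduced.
- Overrun = 15 − 12 = 3 months.
- Share of scheduled time after the last safety test = 3/15 = 20%.

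**Cumulative dose (daily dose × days)**

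| Step | Calculation | mg/kg |
|---|---|---|
| 1 | 0.5 × 30 | 15 |
| 2 | 0.25 × 60 | 15 |
| 3, as written | 0.125 × 360 | 45 |
| Total, as written | 15 + 15 + 45 | 75 |
| Part in months 13 to 15 | 0.125 × 90 | 11.25 |

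- Share of dose after the last safety test = 11.25/75 = 15%.

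**Schedule that fits the trial**

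- Length of the last step = 12 − (1 + 2) = 9 months.
- Total dose = 15 + 15 + 0.125 × 270 = 15 + 15 + 33.75 = 63.75 mg/kg.
- Check: 75 − 11.25 = 63.75 mg/kg.

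**Patients affected**

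The article gives no expected rate of glucocorticoid use. For scale only: each 10% of the 514 planned patients who are prescribed it is 0.10 × 514, about 51 patients.

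**The case against.** The strongest reply is that this is a slip of wording and nobody planned a 15-month course. Every row of Table 1 gives 12 months as its final duration, and the pirfenidone row also puts a build-up before its 12 months, so the authors may use the phrase for the whole regimen and not for the last step alone. Everything else in the article points to 12 months. Drug is handed out at follow-up visits and leftovers are collected at the next allocation, and no allocation after month 12 is described. If the last step was meant to end at month 12, no patient has an untested month of treatment. Even on the literal reading, the overrun is at the lowest dose of an optional drug open to both arms. Arrangements for background medication after the last visit may also stand in the full protocol, which is not shown.

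Much of this stands. A 12-month course is the more likely intent, the safety gap arises only if the cell is followed as written, and the patient count measures no harm because the rate of use is unknown. It does not clear the cell. The first two steps use the same construction to give their own lengths, so the natural reading of the third is 12 further months. The pirfenidone build-up adds days, while this row adds three months. Nor is this a detail left out for brevity: the article states durations that contradict one another, in the table it names as the dosing instruction.

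**Conclusion.** The concern holds. The row prescribes 15 months of glucocorticoid in a trial whose treatment, visits and safety tests end at month 12. If it is followed as written from month 0, 3 of 15 months (20%) and 11.25 of 75 mg/kg (15%) fall after the last planned safety test. The dose figures rest on 30-day months, and the overrun on a month-0 start. The number of patients exposed cannot be derived from the article.

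This is a dosing-instruction error with a limited consequence for safety follow-up. It introduces no bias into the comparison and has no effect on power. It should be corrected because patients are treated from this table and the correction is trivial.

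**What to change.** Reword the last step of the glucocorticoid row as 0.125 mg/kg/day until month 12. This gives 9 months at that dose, 12 months in total, when the drug starts at month 0. Fixing the end point also keeps dosing inside the trial for a patient who starts later. The cost is one table cell.

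If the clinical team does intend 15 months, keep the durations and add a safety visit at the end of dosing (month 15) for glucocorticoid users, both in Table 2 and in the section on information collected at each follow-up. That costs one extra visit for each such patient.
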